### Measures against bias

The study is unblinded with regard to trainers, who hand out the questionnaires at t0 and t1 measurements to the clients. However, t2 telephone interviewers are blind to whether participants belonged to a control or intervention group. A problem of the study may be different selection effects in the groups. Participants of the study may be inclined to follow through a regular training as opposed to potentially less structured treatment as usual. In order to estimate this kind of bias we will analyze models to predict drop-outs in both, the intervention and the control group. In order to prevent trainers from using CAN Stop training elements in their working routine and to unintentionally blur TAU and CAN Stop interventions, trainers of institutions, who were selected into the control group will receive their training for the CAN Stop training intervention only after they completed t1 measurements in young cannabis users. Supervision protocols of CAN Stop trainers for later qualitative analyses will be handled in a way that no inference can be made about the respective trainer.

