Another setting, in which systematic service provision beyond basic structural drug prevention efforts (e.g. general drug use ban etc.) for adolescent and young adult cannabis users is nearly entirely missing, is the juvenile penal system [20]. In Germany, juvenile prisons encompass persons aged 14 to 25 who were convicted under juvenile criminal law. Among the approximately 6500 mostly male young offenders, who are currently serving their prison sentence in Germany, nearly all have experiences with addictive drugs and 60% of incoming juvenile offenders report having used illicit drugs within the past four weeks before serving the prison sentence [21]. Among illicit drugs, cannabis is the most important problem drug [22] and although of course, cannabis use within juvenile prisons is strictly prohibited, ongoing consumption of cannabis takes place. Up to date, we know of no manualized or evidence-based support programme to address cannabis misuse or dependence in adolescent or young adult offenders serving their prison sentence.

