In order to fill the described gaps in the support system for cannabis using adolescents and young adults, our research group developed a structured, manualized group training programme "CAN Stop", which focuses on this specific target group between age 14 and 21, whose needs so far have not been adequately met by the various support system components. The first goal of the project is to provide for an evaluated, evidence-based group programme, which can be easily disseminated and which is tailored to the developmental characteristics and contexts of adolescents and young adults. We hypothesize that young cannabis users who participated at the CAN Stop group training in addition to the treatment or service usually provided in the specific help provision context (e.g. drug addiction aid and youth welfare, in-patient medical context, out-patient medical context, juvenile prisons) show lower level of cannabis intake and higher levels of cannabis abstinence-related self-efficacy after the training as opposed to young cannabis users who received the usual treatment or service. As for the implementation of the programme, we are aware of the existing subdivided and at times confusing help provision system for young cannabis users in Germany, and we believe it is inherent for the effectiveness and for the future dissemination and practicability of the programme, that it is tried out within these different help provision settings. We hypothesize, that because of their above mentioned structural and organizational characteristics, different clientele and context-specific staff will be met within these settings. That is why the programme is implemented and evaluated separately in four different settings (a) the drug addiction aid and youth welfare system, (b) the out-patient medical system, (c) the in-patient medical system and (d) prisons for juvenile offenders. This offers the possibility to check for the suitability of the programme in different settings - our second goal - and to compare its effectiveness and utility within them. Our third goal is to draw conclusions for the future implementation of the CAN Stop training in different help provision settings. Moreover, our fourth goal is to gain knowledge about the incoming clientele of the different settings with regard to their substance use patterns, severity of dependence, psychosocial adjustment, expected effects of cannabis use and family and peer relations. As for the realization of the training programme, this remains in the hand of the existing staff of the different settings. A novelty of the programme is, that no specific prerequisites are prescribed as to the professional background or existing (therapeutic) experience of the trainers. The only exception is the staffs' contact with cannabis using adolescents and young adults as part of their occupation within one of the above mentioned settings and a basic interest to realize the training. This approach may include staff from prison guards, to ex-users working in the addiction aid system to psychotherapists and medical doctors and nurses. With this approach, the introduced study not only evaluates the effectiveness of a group training programme for cannabis using adolescents and young adults (14-21) but also evaluates the instructions given to the trainers, who perform the actual training with the target group, in form of a course of instruction and a newly developed manual. The fifth goal of the project is to evaluate the CAN stop group training programme with regard to its gender-specific utility and effectiveness. Previous therapeutic approaches were evaluated with largely male samples. This may in part be due to the higher prevalences of male cannabis users, but may to some extent also lie in the fact, that previous programmes and approaches were more shaped to address males and were not equally fit to address the specific needs of female cannabis users. The CAN Stop group training was explicitly developed to meet both male and female young cannabis users' needs in that it for example also refers to accompanying internalizing problems and the importance of the dynamics of a romantic partnership with cannabis use patterns - topics which are deemed to address especially female young cannabis users.

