
## Methods/Design

### Study Design and Setting

The CAN Stop study is a four-armed randomized wait-list controlled trial. Following Zwarenstein et al.'s [23] theoretical continuum of evaluation trials, on which rather "experimental", explanatory efficacy-oriented trials form the one end, and naturalistic, pragmatic effectiveness-oriented trials form the other end, this study tends towards the latter, pragmatic end. Developers were more interested in the real-life utility of the CAN Stop group training within the described four different contexts with their aforementioned specificities.

Data will be gathered at three points: before the group training (pre), after the group training (post; 3 months after pre) and at a follow-up (6 months after post). Modes of data retrieval vary from face-to-face interviews and questionnaires (pre), to questionnaires only (post) and telephone interviews and questionnaires (follow-up). Group comparisons will be made to check for the group training's effectiveness.

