### Recruitment of cooperation partners and young cannabis users

Subjects for the study are recruited by cooperating institutions from the settings mentioned above. These cooperation partners were trained by the study group to identify incoming clientele for their eligibility to participate at the study, to perform motivating take-in talks to these young cannabis users, and to gather data for the first two points of measurement (pre and post). The follow-up measurement will be performed by the study group. Moreover, staff of the cooperation partners is instructed to perform the CAN Stop training.

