Both, staff from the cooperating institutions and study participants received incentives for their efforts or taking part in the study, respectively. Data gathering for pre and post measurement by a staff member of the cooperation partner is awarded 10€, the performance of a complete training cycle is compensated with 400€. Young cannabis users receive 10€ for the completion of the pre measurement, 25€ for the completion of the post measurement and 50€ for the completion of a follow-up measurement. Ethical questions arose, whether it is suitable to give out cash to young cannabis users, given the possibility that the money is spent for cannabis. However, we deemed the sum of the incentives for young cannabis users small enough to be compared with money, adolescents and young adults handle in their daily routines and therefore argued that no additional allurement is attached to the incentives. Moreover, previous research with our institution had shown, that cash incentives were more potent and appealing for study subjects ([name], personal communication). If cooperation partners severely objected to this procedure, however, we left the ultimate decision about the nature of incentives to their staff and instructed them to give out gift vouchers e.g. for local music stores instead.

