### Intervention: The CAN Stop group training

The CAN Stop group training consists of eight group sessions à 90 minutes. Groups consist of six to ten young cannabis users and one or two trainers. The group contents and its timeline is described in a detailed manual. Moreover, a general introductory section of the manual provides trainers with background knowledge about cannabis, its effects, aspects of group dynamic as well as recommendations regarding the trainer's attitude towards participants and their consumption. The training's rationale is based on behavioural therapeutic and motivational interviewing elements [24]. It encompasses consumer or craving diaries, the work with social and emotional context variables and potential triggers as well as the elaboration of alternative behaviour strategies and the activation of participants' resources. Generally and for motivational reasons, it is left open to participants within the training whether they want to reduce or stop their cannabis use. However, certain settings at which the training is tested officially require absolute consume stops (e.g. prisons), yet this is a characteristic of the respective institution and not of the training itself. A more detailed description of the training is in preparation. After completing the CAN Stop training, certificates are handed out to participants who, participated at least at five out of eight group training sessions, for further gratification. If within a group, only three or less participants remain after other participants dropped out of the group, the group is not further continued.

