### Training of CAN Stop trainers

The CAN Stop training is performed by cooperation partners' staff. Their professional background may vary starkly with regard to their therapeutical expertise. In order to empower cooperation partners' staff for performing the training, motivating take-in talks and procedures for data gathering, a detailed training is set up, which every trainer has to undergo beforehand. As an effect, our study's goal in essence is, not only to test the effect of the CAN Stop training but also to test the approach to empower cooperations partners' staff to perform the training. Several measures are taken to provide for a sufficient quality assurance with regard to the provision of the CAN Stop training. CAN Stop trainers are asked to record each session on videotape. Videotapes will later be used to check for trainers' adherence to the manual. A special adherence measure was developed, which is oriented closely to the training contents of each session. Regular supervision phone calls with trainers are made by the study group to ensure trainers feel comfortable with their CAN Stop training delivery, and trainers are invited to phone the study group if questions arise, be it regarding contents or regarding difficult social situations within the training or when training participants show signs of acute psychosis or suicidality. Notes are taken of these supervision talks for later qualitative analyses. Identification of these problems and recommendations about how to deal with them are also part of the training of trainers. For further control with regard to the young cannabis users, participants' comfort with the training, participants are asked to indicate their mood shortly at the beginning and end of each training sessions with colour-coded cards. Moreover, participants give feedback on the respective session at the end of each CAN Stop training session with regard to their satisfaction with the training contents and the atmosphere in the group. These data will be gathered and monitored by the study group to ensure that no CAN Stop training runs out of hand.

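### In the juvenile prisons, self-reported cannabis use at t0 and t1 is gathered by the institution that bans it, so it may partly measure willingness to disclose

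*Protocol article*

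**What the plan says.** **Who collects.** Under *Recruitment of cooperation partners and young cannabis users*, the partner institutions are trained "to gather data for the first two points of measurement (pre and post"), and the same part of the article adds: "Data gathering for pre and post measurement by a staff member of the cooperation partner is awarded 10" euros. *Measures against bias* states: "The study is unblinded with regard to trainers, who hand out the questionnaires at t0 and t1 measurements to the clients". The study group itself collects only the follow-up (t2), with telephone interviewers who do not know the arm.

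**Who these people are.** *Training of CAN Stop trainers* says: "The CAN Stop training is performed by cooperation partners' staff". On their background, the last part of *Background* says: "This approach may include staff from prison guards, to ex-users working in the addiction aid system".

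**How.** *Study Design and Setting* says: "Modes of data retrieval vary from face-to-face interviews and questionnaires (pre), to questionnaires only (post"). Table 1 lists substance use history at all three time points. It consists of measures that participants complete, and it contains no biological test.

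**What is at issue in prisons.** *Background* says: "cannabis use within juvenile prisons is strictly prohibited, ongoing consumption of cannabis takes place". The description of the intervention adds: "certain settings at which the training is tested officially require absolute consume stops (e.g. prisons").

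**What is analysed.** *Analysis* plans ANCOVAs with cannabis use and self-efficacy as outcomes and t0 cannabis use as covariate. It predicts larger effects in prisons and out-patient institutions than in in-patient clinics, and more chronic users in prisons and in-patient settings than in out-patient ones.

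**The concern.** In a juvenile prison, a participant who reports current use at t1 reports a prohibited act on a form that comes from, and is gathered by, staff of the institution that prohibits it. Some participants will answer less than fully. This is a reporting problem. It differs from the lack of blinding that the article acknowledges, and it would remain if the staff did not know the arm.

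Three results are at stake:

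- **The arm comparison within prisons.** If the same share of users holds back in both arms, the difference shrinks. If the shares differ, the comparison is biased. Unequal shares are plausible because in the CAN Stop arm the person with the t1 form may be the trainer who has just led eight sessions on this subject. That could make participants more open, or more eager to show success.
- **The comparison between settings.** Under-reporting that is specific to prisons distorts the comparison of effects and of clientele, even when it is equal across arms.
- **The weight of each prison.** Prisoners are not individually randomised; the prison they are sent to decides their arm. With three prisons, a difference between prisons in how forms are handled becomes a difference between arms.

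**Working it through.** The plan gives no figure on disclosure, so there is none to reproduce. The check traces the collection route and then illustrates the possible size.

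**Route in prisons, by time point**

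- t0: interview and questionnaire, gathered by partner staff. The article does not say which of the two carries the use items, nor over what recall period. If they cover use before custody, they do not ask about a breach of the prison ban, and the problem is smaller.
- t1, three months later: questionnaire only, gathered by partner staff. For anyone still detained, recent use is use in custody. The problem is sharpest here.
- t2: collected by the study group, outside this route.

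**Do the planned safeguards cover it?** *Measures against bias* deals with blinding at t2, models of drop-out, and contamination between arms. None of these concerns disclosure to staff at t0 or t1. Adjustment for t0 use does not remove the error, because t0 use comes by the same route. The t2 data do not repair t1, and a change from t1 to t2 also contains a change of collector.

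**Scope.** Partners: 11 + 9 + 8 + 3 = 31, of which 3 are prisons.

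**Illustration.** All rates below are assumptions; none is in the article.

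Reported use = true use × share of users who admit it.

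Take true t1 use of 40% (CAN Stop) and 60% (control), a true difference of 20 points.

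1. Equal admission at share *s*: reported difference = *s* × 20. For *s* = 0.8, 0.6, 0.5 and 0.4 this gives 16, 12, 10 and 8 points. At 0.5: 0.40 × 0.5 = 20% v 0.60 × 0.5 = 30%.
2. CAN Stop participants more open, 70% v 50%: 0.40 × 0.7 = 28% v 0.60 × 0.5 = 30%. The difference falls to 2 points.
3. CAN Stop participants less open, 40% v 50%: 0.40 × 0.4 = 16% v 0.60 × 0.5 = 30%. The difference is 14 points, still 6 below the truth.
4. No true difference, 70% use in both arms. With 60% admission in CAN Stop and 80% in control: 0.70 × 0.6 = 42% v 0.70 × 0.8 = 56%, a spurious benefit of 14 points. With the shares exchanged it is a spurious harm of 14 points.

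Scenario 1 also shows the effect on setting comparisons. With half of users admitting in both arms, a prison effect equal to that of another setting, where use is fully reported, would look half as large. This works against the article's own prediction for prisons.

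These figures treat the outcome as any use, while the plan analyses level of use. They show the mechanism and are no forecast.

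**The case against.** The strongest objection is that the article nowhere says that staff read, check or keep the completed forms. Staff distribute them and participants fill them in. Study codes, sealed return and confidentiality wording normally belong in a full protocol, staff instructions or an information sheet, which are not shown. This stands as a limit on confidence. The point therefore rests on the stated collection route and not on the absence of a safeguard. The article's identity protection for video recordings says nothing about questionnaires either way.

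Other objections also have force. Prisons are 3 of 31 partners. Staff collect in both arms, so a difference in disclosure between arms is plausible but not shown. Prisoners enter the study because of a cannabis problem that is already known at the in-take talk, which may make them more open about earlier use. Follow-up use and self-efficacy are also analysed, and follow-up use comes by a different route.

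A reader might infer more than the documents support:

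- *That honest participants will be sanctioned.* No passage describes sanctions for questionnaire answers.
- *That other partners also require abstinence.* The article speaks of certain settings, but prisons are the only one it names.
- *That staff interview participants about use at t1.* The post measurement is by questionnaire only.
- *That scenario 3 overstates the effect.* It looks large only beside the 10 points of equal 50% admission; against the true 20 points it is an understatement. Upward bias is possible, as scenario 4 shows, but nothing in the article indicates that it will occur.

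**Conclusion.** The point holds for the juvenile prisons at t0 and t1, and chiefly at t1. Every link in the route is stated: partner staff gather the data, guards may be among them, use is banned but continues, and self-reported use is both outcome and covariate. That reported use partly reflects willingness to disclose is an inference from these facts, but a direct one.

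Equal under-reporting attenuates the arm difference in proportion to the share of users who admit use, and distorts prison versus other-setting comparisons. Unequal disclosure could bias the arm difference in either direction. The documents do not allow the direction or the amount to be estimated. The t0 part shrinks if the items concern use before custody.

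Confidence is medium, because the full protocol may already keep the answers from institution staff. The change should be made, or the existing safeguard stated. Once t1 is past, undisclosed use cannot be recovered by the t2 interviews or by covariate adjustment.

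**What to change.** In the prisons, and in any other partner that turns out to require abstinence:

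- At t0, do not ask the cannabis-use items in a staff interview. At t0 and t1, have them self-completed under a study code, sealed by the participant and returned directly to the study group, which already runs t2.
- Use the same procedure in both arms.
- Tell participants in the information sheet that staff of the institution will not see these answers.
- State the recall period of the use items, so that readers can see whether they cover time in custody.

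If the full protocol already does this, one sentence under *Measures against bias* is enough.

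The cost is envelopes, postage and short changes to the information sheet and staff instructions. Staff can no longer check forms for completeness, so a few more items may be missing. Collection in prisons would then differ from that in settings that keep the present route, which should be noted when settings are compared.

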### Ethical considerations

All procedures are in concordance with the ethics committee of the Chamber of Physicians in all federal states of Germany, in which the CAN Stop study takes place. All participants of the study and - in the case of underage young cannabis users - their parents or official guardians are informed about the study goals, procedures, analyses and data reporting prior to participation. Only data of participants who gave written consent will be used for analyses. All young cannabis users of the control group are offered the CAN Stop training after their data gathering is completed. In order to protect young cannabis users' identity to the study group personnel, videographies of CAN Stop training sessions will be made in a way that the camera is focused solely on the CAN Stop trainer - so only voices of young cannabis users are audible on videotapes.

### Analysis

An intention-to-treat approach will be taken to analyze data. Comparisons will be made between intervention group and the TAU control group in the different settings using baseline controlled ANCOVAs with cannabis use and abstinence-oriented self-efficacy as dependent variable and cannabis use at t0 as covariate. We plan to perform nested analyses in order to handle the variance, which is shared between participants attending the same institution. There are no institutions, which offer more than one CAN Stop training group, so a further layer of nesting is not nescessary. We hypothesize that intervention groups show lower levels of cannabis use and higher levels of self-efficacy related to cannabis-abstinence after the intervention as compared to controls. To discover these effects, we calculated the needed sample size of n = 119, assuming a medium effect size of f = 0.25, given the power of the statistical test to .80 and setting the α-error on .05. Prior experience with the target group have shown that attrition rates among young cannabis users are rather high, so we calculated with an attrition rate of 50% when planning the number of nescessary participants at t0. With regard to further effects, we believe there are differences in the effectiveness of the training in the different settings. We hypothesize that the effect of the training (d) will be greater when less other interventions take place in the respective setting, that is, effects are bigger in juvenile prisons and out-patient institutions than in in-patient setting clinics.

Secondary analyses will be made to compare the clientele of the different settings. Here we assume that more aggravated and chronic cannabis users will be found in prisons and in-patient settings than in out-patient settings. As for the role forced access to the group (e.g. because of pressure from juidical institutions or teachers) plays, we believe no differences will be seen between participants, who indicated, they were attending the intervention group because of pressure from outside, as compared to participants, who decided to attend the group solely on their own accord. This is, because we assume the CAN Stop training itself is shaped in a way as to leave decisions about further consume open to participants, which inspires the internal motivation of all participants and therefore blurs differences regarding forced access to the training.

In order to gain insight into the training's utility in the different settings, qualitative and quantitative feedback data from trainers will be synthesized and discussed with clinical experts from different settings for triangulation. Conclusions from this discussion process will be shown to trainers in order to test the plausibility of our conclusions to trainers and to check whether they feel their experiences are sufficiently mirrored in the conclusions.

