In a first attempt to identify suitable cooperation partners, we systematically scanned comprehensive help provision and therapy guides of Northern and Eastern Germany as well as the Internet for institutions. All identified institutions were then invited to participate at the study with an information letter and asked to fax back an attached reply form together with a questionnaire about structural and work details of the institution, such as number of incoming young cannabis users in the targeted age range and number of staff. Prior to this, a target number of cooperation partners needed to gather the subjects was calculated on the basis of a power calculation, an estimated attrition rate of 50% and under the premise that CAN Stop training groups should be composed of six to ten group participants. If feedback was not given within six weeks after letters were sent out, a study group member called to check back with the institution. An exception from this procedure was made within the setting of juvenile prisons: because their total number was rather low, their staffs were contacted directly via phone calls. The response rate varied between different settings between 57% in juvenile prisons, 10% in in-patient medical clinics, 5% in out-patient medical clinics and 5% in the youth welfare and drug addiction aid. If institutions signalled to be in contact with young cannabis users in their daily routines and were interested in study participatioin, a study group member gave a presentation of the project and invited institutions to participate at the study. In sum, we could aquire a total of 11 cooperation partners within the youth welfare and drug addiction aid, 9 cooperation partners of the out-patient medical system, 8 cooperation partners of the in-patient medical system and 3 participating prisons for juvenile offenders. Participating cooperation partners were randomly assigned to perform the CAN Stop intervention plus their usual treatment as an intervention group or to provide for control group subjects, who received the cooperation partner's previously installed treatment as usual (TAU). As for other treatments, provided by the different institutions (besides CAN Stop), cooperation partners differed in their usually provided routines depending on their specific setting. While most prisons indicated, other kinds of therapy besides CAN Stop were rather limited and merely consisted of counselling talks or conceptual work within the organizational framework of the prison, the in-patient medical system's cooperation partners of course provided many other facets of treatment - to mention both extremes of this varying continuum. Institutions, which indicated they were already participating in other structured programmes similar to CAN Stop were excluded from the study in order not to compare CAN Stop with eventually competing studies (e.g. FrED, see above).

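### Comparisons are planned within four settings, but the single n = 119 fits only a total, so power is about .12 to .35 per setting rather than the stated .80

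*Protocol article*

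**What the plan says.** The Background gives the reason for the four-setting structure, namely that clientele and staff are expected to differ: "That is why the programme is implemented and evaluated separately in four different settings". It adds that effectiveness is to be compared between settings and that conclusions for later implementation will follow.

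The Analysis section places the comparison at the same level: "Comparisons will be made between intervention group and the TAU control group in the different settings using baseline controlled ANCOVAs". Cannabis use and abstinence-oriented self-efficacy are the dependent variables. Nested analyses are to deal with variance shared within an institution.

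The sample size follows the hypothesis of lower use and higher self-efficacy in the intervention groups: "we calculated the needed sample size of n = 119". The inputs named for it are f = 0.25, power .80 and alpha .05. The figure is not labelled as a total, per setting or per group. An attrition rate of 50% is then allowed for.

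Setting differences come next, as further effects: "We hypothesize that the effect of the training (d) will be greater when less other interventions take place in the respective setting". Prisons and out-patient institutions are placed above in-patient clinics. No sample size is given for this contrast.

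The recruitment section lists 11 institutions in drug aid and youth welfare, 9 out-patient, 8 in-patient and 3 prisons. It also sets the group size: "CAN Stop training groups should be composed of six to ten group participants". The Analysis section says that no institution runs more than one training group.

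**The concern.** The comparison is described within settings, while the only power statement is a single number with no stated scope. If 119 is the total, each setting has a fraction of it, and .80 does not apply to the comparisons that the Background and Analysis sections describe. The hypothesis about differences between settings needs more information than the main comparison, and has no sample size of its own.

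Two of the stated goals, suitability by setting and conclusions for implementation, rest on setting-level results. With low power, a setting where the training works is likely to give a non-significant result, and differences between settings are mostly noise. A reader who takes .80 to cover these comparisons would give such results too much weight.

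**Working it through.** **Inputs from the protocol.** n = 119, f = 0.25 (d = 0.5 for two equal groups), power .80, alpha .05, attrition 50%, institutions 11/9/8/3 (31 in all), groups of 6 to 10, at most one group per institution.

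**Assumptions, not stated in the protocol.** 1:1 allocation, two-sided test, one covariate, completers split in proportion to institution count, and ICC .05 where clustering is shown.

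**1. The plan's own figure.** Noncentral F with λ = f² × N, numerator df 1, denominator df N − 3. N = 128 gives λ = 8.0 and power .80. N = 119 gives λ = 0.0625 × 119 = 7.44 and power .77. So 119 does not reproduce from the stated inputs. A baseline correlation of about 0.25 would give it (128 × (1 − 0.0625) = 120; 126 × 0.9375 = 118), but none is stated. The steps below do not depend on this.

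**2. What 119 can cover.**
- As a total: 119 / 0.5 = 238 at t0; 238 / 31 = 7.7 per institution, inside the range of 6 to 10.
- Per setting: 119 × 4 / 0.5 = 952 at t0; 952 / 31 = 30.7 per institution. One group each gives 31 × 6 = 186 to 31 × 10 = 310 participants, if control institutions recruit similar numbers.

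Only the total fits.

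**3. Power per setting at f = 0.25.** n = 119 × institutions / 31. The last column uses λ divided by the design effect 1 + (3.84 − 1) × 0.05 = 1.14, with 119 / 31 = 3.84 completers per institution, and denominator df = institutions − 2.

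| Setting | Institutions | n analysed | Power, independent | Power, ICC .05, institution-level df |
|---|---|---|---|---|
| Drug aid / youth welfare | 11 | 42 | .35 | .27 |
| Out-patient | 9 | 35 | .30 | .22 |
| In-patient | 8 | 31 | .27 | .20 |
| Prisons | 3 | 12 | .12 | .06 |

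An equal split (29.75 each) gives .26. Group capacity after 50% attrition (3 to 5 completers per institution), used in place of 119, gives .29 to .44, .24 to .37, .22 to .34 and .10 to .15 in the same order.

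**4. Differences between settings.** SE(d₁ − d₂) = √(4/n₁ + 4/n₂), with unrounded n.
- Out-patient vs in-patient: SE = √(4/34.5 + 4/30.7) = 0.50. A true difference of 0.5 has power .17. The difference detectable with 80% power is 2.80 × 0.496 = 1.39.
- Prisons vs in-patient: SE = √(4/11.5 + 4/30.7) = 0.69. Power for 0.5 is .11. Detectable difference 2.80 × 0.691 = 1.93.

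The detectable differences are about three to four times the assumed main effect of d = 0.5.

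**5. The pooled test.** N = 119, independent observations: .77. With ICC .05, λ = 7.44 / 1.14 = 6.51, and power is .72 with participant-level df (116) or .69 with institution-level df (29).

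**6. Sizing each setting.** 128 × 4 = 512 analysed; 512 / 0.5 = 1024 at t0.

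**The case against.** The strongest reply is that the powered test may be the overall one. The sentence just before the sample size names no setting, and the setting differences follow under a separate heading of further effects. The phrase about different settings could describe only where the data arise. This is a fair reading. For that reason a reader should not conclude that the protocol claims .80 in each setting; it leaves the scope of 119 open. But the Background calls the evaluation separate, no pooled test is named, and the ambiguity itself needs settling.

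That 119 is the total is an inference from group capacity. The conclusion does not depend on it: if 119 per setting was meant, the institutions could not supply it with one group each, and capacity-based power stays at .10 to .44.

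Three stronger readings are tempting, and the document does not support them.
- **Settings will be ranked by d.** The text gives one directional hypothesis, does not clearly place drug aid and youth welfare, and does not rule out an interaction test.
- **Restricted spread in prisons will inflate d there.** No SD is reported. The Background says that use continues in prison, and the Analysis section expects heavier users there, so spread could go either way.
- **Two outcomes in four settings inflate the false-positive rate by a calculable amount.** The document does not say that eight tests each support a claim, and multiplicity rules are commonly left to an analysis plan.

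**Conclusion.** The point holds. The stated .80 does not apply to setting-level comparisons. Power there is about .12 to .35 before clustering, and about .06 to .27 at an assumed ICC of .05 with institution-level df. Between-setting contrasts of 0.5 in d have about 11% to 17% power. These figures rest on the assumed split, 1:1 allocation and two-sided testing. None of the splits examined brings a setting near .80, and three prisons cannot be divided evenly between the two conditions, which lowers power there further. The pooled test also falls short of .80 on the stated inputs, so assigning 119 to it does not by itself rescue the power statement.

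**What to change.** - State that 119 is the number analysed across all settings (238 at t0).
- Make the primary test one model pooled over settings, with setting as a fixed factor and institution as a random effect.
- Identify the prison setting as non-randomised, since the recruitment section says prisoners cannot be randomly allocated, and add a sensitivity analysis without it.
- Restate the power of the pooled test: about .77 at n = 119 with independent observations, about .69 to .72 at an assumed ICC of .05. If a baseline correlation lies behind 119, state it.
- Keep the setting-specific results, since they serve stated goals. Take them from treatment-by-setting terms in the same model, with 95% confidence intervals, and label them exploratory.

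This changes wording and needs no extra participants. The cost is that setting-specific conclusions are no longer confirmatory and that the stated power is lower. Keeping them confirmatory would need about 1024 participants at t0, against a capacity of 186 to 310.
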